**OBJECTIVES AND END POINTS**

**Primary question:** In children 2.00-17.99 years old who present to 6 PERC EDs with acute asthma and have persistent moderate-severe asthma after initial optimal standardized therapy, is there a greater reduction (improvement) in the PRAM score at 120 minutes post- intervention start in those given IVMg (75 mg/kg, max 2.5 g), compared to placebo?

**Primary endpoint:** PRAM score at 120 minutes post start of experimental therapy.

**Secondary questions:** Between these treatment modalities:

a)

b)

Is there a difference in the hospitalization rate for asthma at the index ED visit?

Is there a difference in the hourly changes in the PRAM, respiratory rate, heart rate oxygen saturation and blood pressure from the pre-intervention baseline to 180 minutes?

Is there a difference in the area under the receiver operating characteristic curve for PRAM within 120 minutes?

Is there a difference in the proportion of children achieving PRAM indicating mild asthma status, i.e. ≤ 3 points (widely accepted criterion for discharge home) at 120 minutes?

Does the treatment effect on the primary outcome vary between subgroups defined by: age, sex, pre-randomization PRAM, atopy, non-rhinovirus nasal pathogen36 and “viral-wheeze” phenotype?

Is there a difference in the hospitalization rate for asthma within 72 hours of ED discharge?

Is there a difference in the rate of unscheduled visits for asthma within 72 hours of ED discharge?

Is there a difference in the overall hospital length of hospital stay? Is IVMg a cost-effective treatment option?

c)

d)

e)

f)

g)

h)

i)

**Secondary endpoints:** PRAM, oxygen saturation, heart rate and resp rate 30, 60, 120, 180 minutes and blood pressure 10, 20, 30, 60, 120, 180 minutes after start of experimental therapy and unscheduled medical re-visits/hospitalizations for asthma 72 hours after ED discharge home.

Version Date: June 25, 2025 (v3.0)

Page **14** of **54**

[figure not shown]

**MAGICIAN** Clinical Trial Protocol

**Hypothesis:** Based on a two-tailed hypothesis, children with PRAM ≥ 5 after initial therapy given IV Mg will have a mean PRAM improvement at 120 minutes post IVMg ≥1.0 point greater compared to placebo.

**4.**

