**STUDY DESIGN**

**4.1. Overall Design and the Scientific Rationale for Study Design**

As mentioned above, previous RCTs of IV Mg in children are small and have methodologic limitations. The most recent systematic review (Griffiths, 2016) concludes there is equipoise about IV Mg benefit. More recent large IVMg studies cast doubt on Mg benefit but these have non-RCT designs. Therefore, we propose a 6-centre randomized, double-blind, placebo-controlled trial. Two groups will be compared: IVMg sulfate and IV0.9% saline placebo. After initial therapy with the systemic CSs routinely used for acute asthma management at a given site, 3 treatments with inhaled salbutamol and ipratropium (indications for ipratropium vary by site),52 eligible patients with PRAM ≥5 **(Appendix B: PRAM Score)** will receive a 30-minute IV infusion of 75 mg/kg of Mg sulfate (maximum 2.5 g) [experimental group] or an identical volume of 0.9% saline [control group]. Outcomes will be measured during the 180-minute observational period in the ED and at 72 hours post ED discharge. Primary outcome will be the PRAM score at 120 minutes after start of experimental therapy.

PRAM: PRAM is a validated 12-point asthma severity score53 which exhibits the most comprehensive measurement properties of all asthma scores54 and has been successfully used as an outcome in major trials.3,55 It is the only score with demonstrated criterion validity, using respiratory resistance as the gold standard.25,53 PRAM has been validated in both preschool and school-aged children in the ED with asthma and has strong association with admission.25 PRAM has inter-rater reliability above 70%25 and is adopted in all pediatric EDs in Canada. Most children treated for acute asthma are preschoolers56 who lack coordination to perform pulmonary function tests reliably. To maximize the accuracy of the PRAM measurement, all study nurses will complete online PRAM training module57 at https://enseignement.chusj.org/PRAM-En. We will use an eligibility cut-off of PRAM ≥ 5 post initial therapy as this is associated with clinically concerning respiratory distress requiring further intervention. PRAM ≥ 5 after one hour of initial care has high accuracy (AUC: 0.88) to predict hospitalization.58 Of the 215 children given IVMg in MAGNUM, 118 had PRAM 5, 41 PRAM 6, 35 PRAM 7 and 21 PRAM ≥8 prior to IV Mg.3

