**STATISTICAL CONSIDERATIONS**

**9.1. Sample size**

Sample size is based on the assessment of the PRAM change in the IVMg vs the control group and we *conservatively* aim for an inter-group PRAM difference in change of ≥1.0 point (SD 2.5), based on the following evidence. Children 1-17 years old with a baseline PRAM ≥4 points had a median PRAM change of 3 points if discharged vs.1 point if admitted.25 In a PRAM validation study of children with moderate dyspnea anchored against expert physician-perceived clinical improvement a PRAM change of 1.5 (SD 2.3) was seen for children judged clinically improved vs. 0.0 (SD 2.2) for those unchanged.67 When compared to a change in respiratory rate percentile, a PRAM change of 1.1 (SD 2.7) was seen in the improved patients vs.0.3 (SD 2.2) in those unimproved.67 Based on this evidence, the investigators agree that a minimally clinically significant difference in PRAM changes between groups is 1 point. Although the study non- compliance and loss to follow-up rates in MAGNUM were both 0%, we conservatively assume that the non-compliance (crossover) with allocated therapy and the follow up loss may be as high as 5% and 1%, respectively. Based on these parameters, a study sample of 192 children (96 per group) provides 80% power with a two-sided significance level 0.05. Accounting for the randomization factors of site and age, a sample of 192 children obtained by recruiting in 12 strata (2 ages x 6 sites) with a similar number of children per strata, a significance level of 0.05 and an intracluster correlation coefficient of 0.05, achieves 80% power to detect PRAM difference in change of 1.0 (SD 2.3) based on a mixed-model analysis.

Version Date: June 25, 2025 (v3.0)

Page **24** of **54**

[figure not shown]

**MAGICIAN** Clinical Trial Protocol

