**9.3. Secondary outcome measures**

The two study groups will also be compared with respect to:

1. Hospitalization for asthma at the index ED visit.
2. Changes in PRAM, respiratory rate, heart rate, oxygen saturation and blood pressure from baseline (pre- intervention) to 30, 60, 120, and 180 min and also in blood pressure to 10 and 20 min post-intervention
3. Area under the receiver operating characteristic curve for the PRAM score changes at 30, 60, and 120 minutes.
4. PRAM denoting mild asthma (≤ 3 points is a widely accepted discharge criterion25) at 120 minutes
5. Hospitalization for asthma at any medical facility within 72 hours post- ED discharge.
6. Unscheduled asthma-related visits to any health care provider within 72 hours post- ED discharge.
7. Hospital length of stay.
8. Open label IVMg administration after the 120-minute measurement of the primary outcome.

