**9.7. Secondary outcomes**

For the continuous outcomes changes in the PRAM, respiratory rate, heart rate and oxygen saturation from pre-intervention to 30, 60, 120, and 180 min, a mixed model repeated measures will be conducted with treatment group as the between factor (IVMg vs placebo) and the within factor time 0,60,120,180 min. The analysis will be repeated with the randomization stratification factors site and age. Similarly, blood pressure will be analyzed with the additional time measures at 10, 20 and 30 minutes. For overall hospital stay, the study groups will be compared using the Wilcoxon ranked-sum test. For binary outcomes (hospitalization, PRAM indicating mild asthma, unscheduled asthma-related re-visits), groups will be compared using the chi-square test. For the analysis of the area under the ROC curve for PRAM scores, a mixed model repeated measures ANOVA will be conducted with the between factor study group (intervention vs placebo) and within factor time (30, 60, 120 minutes). In addition to the omnibus test for the group and time factors, an orthogonal polynomial analysis will be conducted to compare trends over time between the study groups.

A comparison based on a logistic regression analysis will be conducted adjusting for the randomization stratification factors site and age. As the secondary analyses are exploratory, overall significance for them will be set at 0.05 (2-sided).

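### The secondary outcome called a ROC area for PRAM names no binary state and does not fit the repeated measures ANOVA specified for it

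*Protocol*

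**What the plan says.** The outcome appears in four places in the protocol.

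- Synopsis (Section 1.1), third secondary objective, and Section 3, secondary question c: "Is there a difference in the area under the receiver operating characteristic curve for PRAM within 120 minutes".
- Section 9.3, item 3: "Area under the receiver operating characteristic curve for the PRAM score changes at 30, 60, and 120 minutes".
- Section 9.7, the analysis: "For the analysis of the area under the ROC curve for PRAM scores, a mixed model repeated measures ANOVA will be conducted". Arm is the between factor of that model, and the three measurement times of 30, 60 and 120 minutes form its within factor. Beyond the omnibus tests, "an orthogonal polynomial analysis will be conducted to compare trends over time between the study groups".

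The input to the area is not constant: PRAM within 120 minutes in the objectives, PRAM changes in Section 9.3, PRAM scores in Section 9.7. No place says which two classes the curve is to separate. Section 9.7 describes the secondary analyses as exploratory.

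**The concern.** A ROC area describes how well a score separates two classes of children. It needs a binary state, and it yields one number for a set of children, not a value for each child. A repeated measures ANOVA with arm as between factor and time as within factor, followed by polynomial trends, needs the opposite: a measurement on every child at every time. Taken literally, the model has no dependent variable.

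An analyst would therefore have to choose the quantity. If that choice came after data by arm had been seen, it would be a post hoc choice among several analyses of a listed secondary objective. One available choice, a ROC area against hospitalization, would say how well PRAM predicts admission and not what magnesium does. Sections 2.1 and 9.2 themselves argue that admission after IV magnesium is driven partly by physician behaviour and confounded by indication.

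**Working it through.** The protocol gives no figure for this outcome, so there is none to reproduce. The check sets what the outcome requires against what the model requires.

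**Inputs.** Two arms and three times (Section 9.7). 192 children, 96 per group (Section 9.1). Design difference 1.0 PRAM point, with SD 2.5 or 2.3 (Section 9.1). PRAM measured at baseline, 30, 60, 120 and 180 minutes (Section 1.2). Where the protocol uses a ROC area properly it names a state, as in Section 4.1: "PRAM ≥ 5 after one hour of initial care has high accuracy (AUC: 0.88) to predict hospitalization". Section 9.2 does the same with hospitalization or long ED stay.

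**What the model needs.** One value per child per time: 192 × 3 = 576 values with full data.

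**What each reading of the outcome supplies.**

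1. *ROC area for one child.* The area is the proportion of positive-negative pairs that the score orders correctly. One child has one state, so the number of pairs is 1 × 0 = 0 and the area is undefined.
2. *Hospitalization as the state.* One area per arm per time gives 2 × 3 = 6 values and 6 − 1 = 5 degrees of freedom. Group takes 1, time 2 and their interaction 2, so 5 − 1 − 2 − 2 = 0 remain for error.
3. *Treatment arm as the state.* Each time then has one area for both arms together. Assuming normal scores with equal SD, it equals Φ(difference / (SD × √2)):
   - SD 2.3: Φ(1.0 / 3.253) = Φ(0.307) = 0.62
   - SD 2.5: Φ(1.0 / 3.536) = Φ(0.283) = 0.61

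   This is a legitimate comparison of arms, but arm has been used to form the area and cannot also be the between factor.
4. *Area under the PRAM-versus-time curve.* This is one value per child, so arms can be compared, but a within factor of time has nothing to act on.
5. *PRAM itself at 30, 60 and 120 minutes.* The ANOVA and the polynomial trends can be run, but the result is not a ROC area. It also overlaps heavily with the PRAM mixed model that opens Section 9.7.

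None of the five readings gives an outcome that is a ROC area and can also be analysed by the stated method.

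**Weights for reading 4.** The intervals are 30, 30 and 60 minutes, so the trapezoid rule gives

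15(P0 + P30) + 15(P30 + P60) + 30(P60 + P120) = 15·P0 + 30·P30 + 45·P60 + 30·P120.

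The weights sum to 15 + 30 + 45 + 30 = 120, so dividing by 120 gives the time-averaged PRAM. Subtracting P0 from that average gives the mean change from baseline.

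**The case against.** Several points on the other side stand.

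- A reader might infer that this outcome cannot be estimated at all. The protocol does not support that. Once a state is named, a ROC area can be computed: hospitalization is recorded, and treatment arm could also serve. What fails is the pairing of this outcome with this model.
- A reader might also infer that any ROC result would describe PRAM as a predictor and say nothing about treatment. That is true with hospitalization as the state. With arm as the state, the area is the Mann-Whitney probability, a valid measure of the treatment effect.
- Nor would early respiratory distress go unreported. Section 9.3, item 2, lists PRAM changes at 30, 60, 120 and 180 minutes, and Section 9.7 gives them their own repeated measures model. The PRAM-time area is a weighted sum of the same scores, so the arm difference in its mean follows from the arm differences at each time. Only the single summary number is missing.
- The contested ANOVA is not an exact duplicate of that first model, whose listed time factor is 0, 60, 120 and 180 minutes. The contested one includes 30 minutes and adds polynomial trends.
- A statistical analysis plan not at hand might define the quantity. The protocol wording would still need correcting to agree with it.

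The mismatch itself survives. The ROC term is spelled out in three places and abbreviated in a fourth, so it is not a single typing slip, and no section supplies the missing state.

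**Conclusion.** The point holds as an incompatibility between a named secondary outcome and its stated analysis: no binary state is given, and a ROC area cannot supply one value per child per time. The finding is structural and does not depend on any assumed effect or variance. The normality assumption affects only the illustrative 0.61 to 0.62.

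It should be fixed but is not critical. It touches one of eight secondary outcome measures, in a set called exploratory. The primary endpoint, sample size, interim analysis and safety monitoring are unaffected.

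The limit to 120 minutes and the serial time points suggest that the area under the PRAM-versus-time curve was meant. That is inference: the protocol does not say so, and the time factor and polynomial trends point equally well to PRAM over time.

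**What to change.** Before unblinding, the sponsor should state the intended quantity and use it identically in the synopsis, Section 3, Section 9.3 and Section 9.7. Either repair is coherent.

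**(a) Area under the PRAM-versus-time curve, 0 to 120 minutes.** One value per child, (15·P0 + 30·P30 + 45·P60 + 30·P120) / 120, less P0 if change from baseline is meant, as Section 9.3 suggests. Compare arms by a t-test and by a linear model with site and age group, as Section 9.6 does for the primary outcome. Adding baseline PRAM as a covariate would be preferable, but Section 9.6 does not currently include it. Drop the time factor and the polynomial contrasts for this outcome.

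**(b) PRAM over time to 120 minutes.** Keep the repeated measures model and the polynomial trends, rename the outcome, remove the ROC wording, and acknowledge the heavy overlap with the PRAM mixed model at the start of Section 9.7.

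The cost is wording in four places. No measurement is added, because PRAM is already recorded at baseline, 30, 60 and 120 minutes.

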**9.8. Measurement of outcomes at follow up**

Trained and intervention-blinded research nurses will measure PRAM, respiratory rate, oxygen saturation and blood pressure pre-randomization and at the above intervals, up to 180 minutes post starting the intervention, ascertain disposition and other pharmacotherapy given in the ED and determine other outcomes via automatic REDCap e- mails/study team e-mail/telephone at 72 hours post-ED discharge. If there has been no response, there will be daily reminders until day 7.

**9.9. Safety outcomes**

Each adverse event will be described as per good clinical practice guidelines. Descriptive statistics will be used to report frequencies of adverse events and SAEs in the groups. If appropriate, differences between the groups will be compared using a two-sample t-test or Wilcoxon rank sum test. These analyses will be reviewed by Data and Safety Monitoring Committee (DSMC) every 6 months.

***Missing Data:*** Missing data will be imputed using multiple imputation. Analysis

Version Date: June 25, 2025 (v3.0)

Page **27** of **54**

[figure not shown]

**MAGICIAN** Clinical Trial Protocol

will be done using SAS™ software.

**9.10.**

**Interim analysis**

Given the long study timeline, one interim analysis is planned after we recruit 50% of our sample. We will follow the O’Brien-Fleming group sequential method with a level of significance of 0.0054 at the interim analysis and 0.0492 for the final analysis. This analysis will be conducted by the statistician assigned to the DSMC (not otherwise involved in the trial) and evaluated by the DSMC.

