**6.5. Measures to Minimize Bias: Randomization and Blinding**

**Treatment allocation:** The leading site pharmacy will use the randomize.net tool to produce the study Master Randomization tables, stratified by site and age group (< 6years old, i.e. prior to 6th birthday vs ≥6 years old as pre-schoolers may respond differently to asthma therapies),52 employing permuted randomization of varying block sizes in a 1:1 ratio of Mg sulfate to placebo. The study nurse will transcribe the assigned study kit numbers into the secure Health Canada-validated REDCap database.

Master lists will be provided to all participating research pharmacies which will permit the preparation of the study kits according to the randomization schedule.

Version Date: June 25, 2025 (v3.0)

Page **20** of **54**

[figure not shown]

**MAGICIAN** Clinical Trial Protocol

The patients, outcome assessors (study nurses, ED physicians) and investigators will be blinded to treatment assignment; the pharmacy will be unblinded. The SickKids research pharmacist will provide a manual with instructions on how each pharmacy will prepare blinded numbered kits with Mg or 0.9% saline placebo, according to routine IVMg sulfate infusion protocols (**Section 6.4.3 Logistics of Blinding and Kit Making)**. Each site will receive requirements for drug accountability and handling. Unblinding is unlikely and did not occur in MAGNUM. The active Mg and saline placebo are identical in volume, color, odor, and appearance. Further, children with unstable airway will be excluded and only 6% experience a mean BP drop 5mmHg after IVMg with fewer requiring intervention.10

Administration of open-label IV-Mg would highly increase the probability of study contamination and will be strongly discouraged until after 120 minutes after the start of the experimental therapy. Children not responding to/worsening after the experimental therapy will be given back-to-back administration of inhaled salbutamol, other required medications and supplemental oxygen if necessary. In the highly exceptional event of impending respiratory failure after the intervention (children with unstable airway on arrival will be excluded), immediate open-label IVMg will be permitted with locally used Mg doses, but unblinding will not be needed because a 2nd Mg infusion is safe for normotensive patients.47-49,51,60 (**Section**

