**9.6. Primary outcome**

For the primary outcome of the change in PRAM at 120 minutes, the study groups will be compared using the Student’s t-test. A comparison based on a multiple regression analysis will be conducted adjusting for the randomization stratification factors site and age.

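### The interim and final significance levels (0.0054 and 0.0492) use too small an O'Brien-Fleming constant and give an overall two-sided type I error of 5.13%, not 5%

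*Protocol*

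**What the plan says.** Protocol section 9.10 states that "one interim analysis is planned after we recruit 50% of our sample", and that the trial will follow the O'Brien-Fleming group sequential method with a "level of significance of 0.0054 at the interim analysis and 0.0492 for the final analysis". The analysis is done by the DSMC's statistician and evaluated by the DSMC.

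Section 9.10 gives no overall alpha. The only one on offer is in section 9.1, where the sample of 192 "provides 80% power with a two-sided significance level 0.05". The hypothesis in section 3 is also two-tailed. Section 9.6 names the primary comparison, a Student's t-test on the change in PRAM at 120 minutes. The protocol names no spending function and no other information fraction.

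**The concern.** One look at half the information, the O'Brien-Fleming form and an overall two-sided 0.05 together fix both levels, so nothing is left to choose. The printed levels are not the ones that follow, and together they spend more than 0.05.

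The method named and the numbers printed therefore give two different thresholds for the primary endpoint. A statistician who computes the O'Brien-Fleming boundary tests the final analysis at 0.0480. One who reads the text tests at 0.0492. A final p-value between the two would be positive under one reading and negative under the other. Section 2.1 says the result will lead either to routine early use of intravenous magnesium or to its de-implementation, so the threshold should not be open to argument once the data are in.

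**Working it through.** **Inputs**

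- Overall two-sided alpha: 0.05 (section 9.1)
- One interim look at 50% of recruitment, then the final analysis (section 9.10). The primary endpoint is read at 120 minutes in the emergency department, so the information fraction is taken as t = 0.5.
- Stated levels: 0.0054 and 0.0492 (section 9.10)
- Primary test: t-test on PRAM change (section 9.6), treated as normal and then checked with the t distribution

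**Step 1: critical values of the stated pair.** The two-sided level 0.0054 corresponds to |z| > 2.782, and 0.0492 to |z| > 1.967. Their ratio is 2.7822 / 1.9669 = 1.4145. The classical O'Brien-Fleming boundary with two equally spaced looks has c₁ = C√2 and c₂ = C, a ratio of 1.4142. With C = 1.967 the interim level is 0.0054, so the plan's pair is reproduced as an O'Brien-Fleming boundary. What remains is the overall level that this constant gives.

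**Step 2: overall type I error of the stated pair.** Under the null, (Z₁, Z₂) is bivariate normal with correlation √0.5.

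α = 1 − P(|Z₁| < 2.782, |Z₂| < 1.967) = 0.0513

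Of this, 0.0054 is spent at the interim, and 0.0513 − 0.0054 = 0.0459 at the final analysis without an earlier stop. A simulation of 20 million normal draws gives 0.0513. A simulation of 4 million t-tests at 96 and then 192 children gives 0.0514.

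**Step 3: the constant that gives 5%.** Solving 1 − P(|Z₁| < C√2, |Z₂| < C) = 0.05 gives C = 1.9774.

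| Boundary at t = 0.5 | Interim level | Final level | Overall alpha |
|---|---|---|---|
| As stated in 9.10 | 0.0054 | 0.0492 | 0.0513 |
| O'Brien-Fleming, overall 0.05 | 0.0052 (z = 2.797) | 0.0480 (z = 1.977) | 0.05 |
| Lan-DeMets, O'Brien-Fleming type, 4{1 − Φ(z₀.₉₈₇₅/√t)} | 0.0031 | 0.0490 | 0.05 |
| Spending 2{1 − Φ(z₀.₉₇₅/√t)} | 0.0056 | 0.0478 | 0.05 |
| Interim kept at 0.0054 | 0.0054 | 0.0479 | 0.05 |
| Final kept at 0.0492 | 0.0026 | 0.0492 | 0.05 |

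**Step 4: other explanations**

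- *Rounding.* Moving both stated levels across their rounding range gives 0.0512 to 0.0514.
- *One-sided levels.* Read that way, the pair spends 0.0509 one-sided, and the protocol says two-sided.
- *A different timing.* The overall error is 0.0520 at t = 0.4, 0.0506 at t = 0.6 and 0.0500 at t = 0.70. The pair holds 5% only if the look comes at about 70% of the information or later. These fractions are assumptions for illustration; section 9.10 says 50%.

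**Step 5: cost in power.** For a trial with 80% power at two-sided 0.05 without an interim look, group-sequential power is 80.0% with the stated pair and 79.7% with 0.0052/0.0480. With 96 per group, a difference of 1.0 and SD 2.5 from section 9.1, before any allowance for crossover or loss, it goes from 79.1% to 78.8%.

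**The case against.** The strongest reply is that the boundary is of the right kind and the error is trivial. The ratio of the critical values is √2 to three decimals, so the named method was used and only its constant is off. The excess is 0.13 percentage points. Under the null, the chance of passing the interim and then landing between 0.0480 and 0.0492 is about 0.12%. No patient number, date or procedure changes. Section 9.10 also claims no overall alpha, so the 0.05 is inferred from section 9.1.

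Much of this is fair. The fault is the constant, not the type of boundary, and it is small. Taking 0.05 as the overall level is an inference, though the protocol offers no other level. None of this makes the printed pair correct. A prespecified alpha is a guarantee, and the protocol itself prints the levels, so a later analysis plan would have to repeat the error or contradict the protocol.

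Two further replies narrow the point. Quoting 0.05 in the sample-size paragraph is not a second error: with the stated pair, power is the same to one decimal as for a fixed design at 0.05 (79.1%). Moving to a spending function is an option, not a necessity.

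**Conclusion.** The levels are wrong as written. With one look at half the information, 0.0054 and 0.0492 give an overall two-sided type I error of 0.0513 against the 0.05 in section 9.1. The O'Brien-Fleming levels for 0.05 are 0.0052 and 0.0480. This rests on taking 0.05 as the overall two-sided level, on an information fraction of 0.5, and on a boundary with no compensating rule, since the protocol states none. The size is 0.13 percentage points of alpha, and it affects the conclusion only for results close to the threshold. It should still be corrected before the interim look, because afterwards a change of threshold could look like a choice of answer.

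**What to change.** In section 9.10, restate the levels as 0.0052 at the interim and 0.0480 at the final analysis, and say that the overall two-sided level is 0.05. Give the critical values (2.797 and 1.977) or one more decimal (0.00517 and 0.04799) as well, because the four-decimal levels taken literally sum to 0.05002.

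Alternatively, name the Lan-DeMets O'Brien-Fleming-type spending function, which gives 0.0031 and 0.0490 at exactly 50%. The levels can then be recalculated for the number actually analysed at the interim.

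Whichever is chosen, use the same final level in section 9.1, in the DSMC charter and for the primary confidence interval. The cost is two numbers and about 0.3 percentage points of power with the classical pair. This correction alone calls for no change in sample size.
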